### 5.6 Follow-up visits

Patients will return for follow-up visits, once every 4 weeks over a 24-week period after enrollment. During these visits, patients will meet with the diabetes educator and have their insulin pump parameters (basal rate, carbohydrate to insulin ratio for meals, etc.) adjusted according to their SMBG and trends observed from the RT-CGM.

The blood glucose measurements of patients will be reviewed by the study staff on a weekly basis using the CareLink system and suggestions for insulin pump adjustments will be provided to the patient via the phone or during a study visit. In addition, symptoms of gastroparesis will be managed according to the prevailing standard of care including appropriate use of antiemetic and prokinetic medications as outlined in SOP IV: Standard of Care for Patients with Diabetic Gastroparesis.

**Week 4 visit:** Patients will meet with a diabetes educator to review blood glucose levels and to make necessary adjustments to insulin doses through the insulin pump. The Follow-up Medical History form will be completed. Any unanticipated adverse events will be reviewed with the patient and recorded on case report forms.

**Week 8 visit:** Patients will meet with a diabetes educator to review blood glucose levels and to make necessary adjustments to insulin administration by adjustment of parameters of the pump. The Follow-up Medical History form will be completed. Any unanticipated adverse events will be reviewed with the patient and recorded on case report forms.

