#### Mild hypoglycemic episodes

For a **hypoglycemic event** to be considered mild; the capillary glucose will be 50 - 70 mg/dL as confirmed by a finger stick glucose meter reading (SMBG); and the patient is fully capable of self treatment without the need of third party assistance. Mild hypoglycemia may be symptomatic or asymptomatic. The following treatment protocol for mild hypoglycemic episodes will be followed:

1. If the SMBG value is 50 - 70 mg/dL, it should be treated by ingestion of 15-20 grams of carbohydrates (e.g., 4-5 glucose tablets, 5-6 Lifesavers, 4-6 oz. of a regular [non diet] soft drink, or 8 oz. low fat milk, or 4 teaspoons of sugar dissolved in a liquid or juice). If the subject is in the hospital, the SMBG reading will be confirmed by a laboratory glucose measurement, but treatment will be initiated based on the Ultra reading.
2. Blood glucose should be self-tested 15-20 minutes after ingestion of carbohydrates and therapy will be repeated as above, as needed. Cycle should be repeated until glucose level is 80 mg/dL or above.
3. Once episode is resolved, if no meal is scheduled the next 2 hours, a mixed nutrient snack, including a carbohydrate, protein, and fat will be ingested right after the initial therapy and after resolution of episode to prevent another episode.

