#### Moderate hypoglycemic episode

For a **hypoglycemic event** to be considered moderate, the capillary glucose will be below 50 mg/dL using a finger stick glucose meter reading (SMBG), and the patient is fully capable of self-treatment, without

the need of third party assistance. The following protocol for treatment of **moderate hypoglycemia** will be followed:

1. If blood glucose level is less than 50 mg/dL, the patient should ingest 30 grams of carbohydrates (e.g., 6-8 glucose tablets). If the subject is in the hospital, the Ultra glucose reading will be confirmed by a laboratory glucose measurement, but treatment will be initiated based on the SMBG reading.
2. The capillary blood glucose will be tested 15-20 minutes after ingestion of carbohydrate and therapy will be repeated as above, as needed, and repeated until glucose level is 80 mg/dL or above.
3. Once the episode is resolved, if a meal is not scheduled within the next 2 hours, a mixed nutrient snack, including carbohydrate, protein, and fat should be ingested right after resolution of episode to prevent another episode.

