### **Severe hypoglycemic episodes**

If the capillary glucose level is below 50 mg/dL by an finger stick glucose meter reading (SMBG), and the patient is incapable of self-treatment, hence in need of assistance from a third party (friend, relative, paramedic, etc), the following treatment protocol will be followed:

For patients that are conscious and cooperative and NOT in the Hospital, Clinic or ER:

1. Turn patient on side and administer 1 mg of glucagon (intramuscular, subcutaneous, or intravenous) using the provided kit.
2. Check SMBG value in 10 minutes.
3. If consciousness and cooperation are fully restored and finger stick glucose value is above 80 mg/dL, provide with 20 grams of sugar (e.g., 4-5 glucose tablets, 5-6 Lifesavers, 4-6 oz. of a regular [non diet] soft drink, 8 oz. low fat milk, 4 teaspoons of sugar dissolved in a liquid or juice) and check glucose level again in 20 minutes.
4. If the SMBG value is partially restored >60-80 mg/dL but patient remains conscious and fully cooperative, provide patient with another 20 grams of carbohydrate and repeat cycle until finger stick glucose value is >80 mg/dL and stable.
5. If SMBG value is NOT above 60 mg/dL at the 10 minute check, call 911. If patient is still cooperative, offer 20 grams of carbohydrate; repeat cycle until paramedics arrive.

For patients that are unconscious or neurologically impaired and NOT in the Hospital, Clinic or ER:

1. Turn patient on side and administer 1 mg of glucagon (intramuscular, subcutaneous, or intravenous) using the provided kit.
2. Call paramedics or 911 (if haven't already done so).
3. Check finger stick glucose value in 10 minutes.
4. If consciousness and cooperation are fully restored and finger stick glucose value is above 80 mg/dL and paramedics have NOT arrived, provide patient with 20 grams of sugar (e.g., 4-5 glucose tablets, 5-6 Lifesavers, 4-6 oz. of a regular [non diet] soft drink, or 8 oz. low fat milk, 4 teaspoons of sugar dissolved in a liquid or juice) and check glucose level again in 10 minutes, and provide with a mixed nutrient drink. Check finger stick glucose value every 10 minutes until paramedics arrive.

Whenever possible, all hypoglycemic glucose values will be confirmed by a laboratory glucose measurement, if the subject is in a setting where a laboratory glucose measurement can be obtained.

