### 7.1 Definitions

**Adverse event:** An adverse event is any untoward medical occurrence that may present itself during a research study which may or may not have a causal relationship with the treatment or study participation. Adverse events include any unanticipated problems involving risks to participants, or breaches of protocol which might entail risk to participants. The term “unanticipated problem” includes both new risks and increased occurrence of anticipated problems.

**Severe hypoglycemic events** occur when a patient’s capillary glucose falls below 50 mg/dL and the patient is incapable of self treatment, hence needing the assistance of a third party (friend, relative, paramedic, etc) for resolution of the hypoglycemia. This type of event will be recorded on study form(s). If a patient has more than two severe hypoglycemic events (i.e., ER visit, relative, etc.) during the study, he/she will be re-evaluated with the diabetologist with an option to be placed back on the previous diabetes medications or insulin regimen. Study staff will follow up with patients to ensure that severe hypoglycemic events were properly managed and make any necessary modifications to their treatment.

**Severe hyperglycemic events** occur when a patient’s capillary glucose is above 500 mg/dL as revealed on an finger stick reading (SMBG, confirmed by a reference glucose value if available) and/or a blood ketone test of 0.6 mmol/L or higher and/or the presence of nausea, vomiting or altered mental status. The patient may be symptomatic (polyuria, polydipsia) or with concurrent illness, but capable of good communication or the patient’s symptoms may be intense, or the patient is incapable of good communication and immediate transport to emergency department may be necessary. These severe hyperglycemic events will be recorded on study case report forms according the procedures for SAEs in Section 7.3.

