### 7.2 Adverse event reporting

Adverse events will be recorded on case report forms if they are thought to be associated with GLUMIT-DG study participation in accordance with the adverse event definitions. Adverse events may be discovered during regularly scheduled visits or through unscheduled patient contacts between visits. Summary data on adverse events will be reviewed by the GLUMIT-DG Safety Officer and Executive Committee monthly and will be monitored by the GpCRC DSMB quarterly or more frequently, as needed. These summaries will include analyses comparing rates of adverse events by clinic or in other subgroups requested by the DSMB.

After each meeting of the DSMB, the NIDDK will issue a letter to the investigators regarding the recommendations and advice given to the NIDDK by the DSMB. This will include information about the review of the study data, including adverse events. Investigators will be responsible for transmission of this letter to the IRB at each of the study centers. Analyses or listings of adverse events will not be provided to the IRBs; however, adverse events involving unanticipated problems involving risks to participants, or breaches of protocol which might entail risk to participants will be reported to local IRBs as soon as possible after they are discovered. Each participating center is responsible for ensuring that all local IRB requirements for reporting adverse events are met.

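### Hypoglycaemia grades leave some assisted episodes unclassified and conflict with the synopsis outcome; adverse-event recording depends on relatedness although the definition does not

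*Protocol*

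**What the plan says.** **Hypoglycaemia.** Section 6.2 sets three grades, each with two conditions that must both hold.
- Mild: a meter value of 50-70 mg/dL, "as confirmed by a finger stick glucose meter reading (SMBG); and the patient is fully capable of self treatment".
- Moderate: "the capillary glucose will be below 50 mg/dL using a finger stick glucose meter reading (SMBG), and the patient is fully capable of self-treatment".
- Severe: a meter value below 50 mg/dL in a patient who needs a third party. Section 7.1 repeats this: "capillary glucose falls below 50 mg/dL and the patient is incapable of self treatment".

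Section 7.1 makes every severe hypoglycaemic event an SAE. It defines sentinel events as a subset of SAEs, again tied to a value below 50 mg/dL. Section 8.2 counts mild, moderate and severe events from discrete glucose values and refers back to the earlier definitions.

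The synopsis (Outcome measures) words the primary outcome differently. Mild or moderate episodes are those below 70 mg/dL on the home meter and/or a hospital reference value, with no mention of self-treatment. It adds the absolute number of severe episodes, without defining severe.

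**Adverse events.** Section 7.1 defines an adverse event whether or not it is causally linked to treatment or participation. Section 7.2 states: "Adverse events will be recorded on case report forms if they are thought to be associated with GLUMIT-DG study participation". The text for each follow-up visit in Section 5.6 states: "Any unanticipated adverse events will be reviewed with the patient and recorded on case report forms".

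**The concern.** This is an uncontrolled, open-label study whose principal objective is safety, and hypoglycaemia is its primary outcome. The definitions decide what is counted, so a gap or a conflict in them feeds directly into the result.

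The gap lies among episodes where the patient could not cope alone. The same counts are used elsewhere: in the DSMB's analysis of percent increase (Section 8.4), in automatic SAE status and expedited sentinel review (Sections 7.1 and 7.3), and in the re-evaluation provision tied to the number of severe events (Section 7.1).

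On adverse events, there is no control arm against which to judge cause. Deciding relatedness before an event is written down is therefore a weak filter, and one applied separately at each of seven centres.

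**Working it through.** No figure in the protocol has to be reproduced; the check sets the definitions side by side. I take the reference in Section 8.2 to an earlier section on safety monitoring to mean Sections 6.2 and 7.1. The synopsis item of that name contains no episode definitions.

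**Step 1: enumerate glucose against assistance.**

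| Episode | Grade under 6.2/7.1 | Synopsis primary outcome | SAE by being graded severe |
|---|---|---|---|
| Below 50, self-treated | Moderate | Counted | No |
| Below 50, assisted | Severe | Counted, severe | Yes |
| 50-70, self-treated | Mild | Counted if below 70 | No |
| 50-70, assisted | None | Counted if below 70, not as severe | No |
| No value from any source, assisted | None | Not counted | No |

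The fourth row is the conflict: one event is inside or outside the primary outcome depending on the section applied. The fifth row is the gap: neither wording counts it. Neither row reaches the severe count.

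**Step 2: can the fifth row occur?** For severe episodes outside hospital, the steps in Section 6.2 begin with glucagon, and the first glucose check listed comes 10 minutes later. The section presupposes a reading below 50 mg/dL, but no listed step obtains one before treatment. A qualifying value may therefore never be documented.

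**Step 3: follow the SAE and sentinel rules.** An ungraded assisted episode can still be an SAE under the general criteria in Section 7.1 (death, threat to life, hospitalisation, disability) or by medical judgment. It is not one automatically. Sentinel status requires a value below 50 mg/dL as well as an outcome such as loss of consciousness. An unconscious patient with no such value does not meet the sentinel definition, even if the event is reported as an SAE.

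**Step 4: compare the adverse-event rules.**
- Definition (7.1): independent of cause.
- Entry on case report forms (7.2): only if thought associated with participation, although the same sentence appeals to the definitions.
- Visit text (5.6): names unanticipated events only.
- Unanticipated problems (7.1): these include a rise in the frequency of anticipated ones. Such a rise cannot be seen reliably unless anticipated events are recorded routinely.
- Summaries (7.2): adverse-event rates are compared by clinic. With relatedness as an entry condition, differences between clinics mix true rates with local judgment.
- SAEs (7.3): all are reported, with no relatedness filter.

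The relatedness condition therefore bites mainly on non-serious events.

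**Step 5: size.** Planned exposure on treatment is 40 x 24/52 = 18.5 patient-years. This is exposure, not loss. The protocol gives no frequency for assisted episodes at 50-70 mg/dL or without a value, so the number affected cannot be derived.

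**The case against.** The strongest reply is that most events still have a route into the data, and much of it stands.

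- A reader might infer that any assisted episode without a home-meter reading leaves the primary outcome. The documents do not support that. The synopsis and Section 8.2 accept hospital or laboratory values, Section 6.2 asks for laboratory confirmation where it can be had, and the synopsis wording captures assisted episodes at 50 to below 70 mg/dL. The sample size rests on mild, moderate and severe episodes pooled, so misgrading alone does not change that total.
- A reader might infer that the gravest hypoglycaemia goes unreported. Fatal, life-threatening or hospitalised cases are SAEs at any glucose value, and all SAEs are reported.
- A reader might infer that device harms cannot be estimated. Section 6.1 itself attributes infection, haematoma and skin reactions to the sensors and infusion sets, so most would pass a relatedness filter. Appendix 11.2 also schedules adverse event monitoring at every visit without qualification, and Section 5.6 does not forbid recording other events.
- Requiring a documented glucose value is a defensible objective criterion in an open-label study.

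These replies limit the damage but do not remove the conflicts. The synopsis and Sections 6.2, 7.1 and 8.2 still give different counts for the same episode. An assisted episode with no value still counts nowhere. Section 7.2 still adds a condition that Section 7.1 excludes.

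**Conclusion.** The point holds in two parts. First, Sections 6.2 and 7.1 leave assisted episodes at 50-70 mg/dL, or with no value, ungraded and outside automatic SAE and sentinel status, and the synopsis disagrees with them about the primary outcome. The absolute number of severe episodes can be understated. Second, the recording rules in Sections 7.2 and 5.6 are narrower than the adverse-event definition in Section 7.1. This mainly affects non-serious events and makes rates by clinic depend on local judgment.

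It is tempting to conclude that the primary comparison is biased toward safety. The documents do not show this. The test concerns change from baseline, and no section applies different episode definitions in the two periods, so events could be lost in both. The size is unknown, and the 18.5 patient-years indicate only how limited the exposure is. The conclusion assumes that sites apply the text literally and that Section 8.2 refers to Sections 6.2 and 7.1. The matter should be corrected, because it touches the primary outcome and the remedy is cheap.

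**What to change.** 1. Reconcile the synopsis (Outcome measures) with Sections 6.2, 7.1 and 8.2 so that every assisted episode falls in a stated category, both for outcome counting and for SAE and sentinel reporting. The sponsor and clinical investigators must settle the category; no new glucose threshold is proposed here, and the treatment steps stay as they are.
2. List assisted episodes with no glucose value from any source separately, for the baseline and treatment periods, so that they are visible whatever the main count does.
3. In Sections 7.2 and 5.6, record all adverse events at every visit, with relatedness and expectedness as data fields and not as conditions for entry. This agrees with the definition in Section 7.1 and the schedule in Appendix 11.2.

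The cost is protocol and case-report-form wording, plus modest extra data entry for 40 patients. If the reconciled category changes which events are severe, the Section 7.1 provisions that depend on the severe count need to be read again for consistency.

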### 2.1 Introduction

Gastroparesis is a disorder of gastric neuromuscular sensory and motor function that affects patients in the prime of their life. Gastroparesis is a devastating disease affecting predominantly young women (females outnumber males by a ratio of 4:1, with an average 34 years of age). The symptomatic profile of gastroparesis includes nausea (90% of patients), vomiting (>80%), pain (~50%), early satiety (60%), and bloating (75%) and can vary in both the combination of symptoms and their severity. Because of its chronic and often intractable nature, the disorder has a tremendous impact on both patients and society at large. Gastroparesis remains difficult to treat, in large part because of the lack of knowledge of the underlying pathophysiology of this disease. Several factors, in particular, have impeded the progress in this field including the paucity of patients seen by any one center, the absence of uniform diagnostic criteria, the lack of generally available, reliable methods for physiological testing and the inaccessibility of tissue for histopathological correlation.

The Gastroparesis Clinical Research Consortium (GpCRC) is a cooperative network of seven clinical centers and one Data Coordinating Center (DCC) supported by the National Institute of Diabetes and Digestive and Kidney Diseases (NIDDK), through the mechanism of RFA-DK-05-004, established in 2006. Clinical centers are responsible for proposing protocols, participating in their overall development, recruiting patients, conducting the research, and disseminating research findings. The individual clinical centers participate in a cooperative and interactive manner with one another and with the DCC in all aspects of the GpCRC. The DCC supports protocol development; provides sample size calculations, statistical expertise, forms, and data analysis; supports manuscript preparation; and provides overall study coordination and quality assurance, including coordination of the activities of the Data and Safety Monitoring Board, the Steering Committee and other standing committees.

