#### Mild hyperglycemia episodes

For a **hyperglycemic event** to be considered mild, the capillary glucose will exceed 180 mg/dL up to 300 mg/dL using a finger stick glucose meter reading (SMBG) and there are no blood or urine ketones present and the subject is not nauseated, vomiting or having an altered sensorium. For mild hyperglycemia the following treatment protocol will be followed:

1. The pump settings have been set up to provide extra amounts of insulin as "boluses" based on target for glycemia and estimated insulin sensitivity index (so-called correction factor) as well as estimated residual insulin from previous boluses (proprietary calculation of Medtronic). Patients will be asked to check blood sugar 1 hour following correction to assess effectiveness of correction. In the event the glucose does not drop by 50 mg/dL or more in one hour patients will be asked to use bolus wizard to determine correction dose but not deliver the dose, disconnect from the pump and deliver the calculated dose using a syringe or insulin pen. They will then be asked to change the insulin in the reservoir, the tubing and the infusion set, and continue to monitor blood glucose hourly, until blood glucose is less than 180 mg/dL.

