#### Moderate hyperglycemia episodes

For a hyperglycemia event to be considered moderate, the capillary glucose will exceed 300 mg/dL up to 500 mg/dL using a finger stick reading (SMBG). The treatment protocol should be followed:

1. If patients are symptomatic or mildly symptomatic, they will be requested to contact the diabetes educator or diabetologist and decisions will be made via the telephone (self adjustment, a visit to the study doctor, or an emergency department visit) based on individual circumstances.
2. Patients with type 1 diabetes will be required to test themselves for ketones using the ketone-meter strips provided to them. If the ketonemia is equal or greater than 0.6 mM/L, the patient will be requested to change the infusion setting of the pump and additional insulin may be provided with injections to avoid further progression into ketoacidosis. Patients will be asked to check blood sugar with SMBG 1 hour following correction to assess effectiveness of correction. In the event the glucose does not drop by 50 mg/dL or more in one hour patients will be asked to use bolus wizard to determine correction dose but not deliver the dose, disconnect from the pump and deliver the calculated dose using a syringe or insulin pen. They will then be asked to change the insulin in the reservoir, the tubing and the infusion set, and continue to monitor blood glucose hourly, until blood glucose is less than 180 mg/dL and blood ketones are less than 0.6 mM/L.
3. If the glycemia and ketonemia do not improve or worsen or the endocrinologist judges it necessary, the patient will be requested to visit the emergency department.

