#### Severe hyperglycemia episodes

For a **hyperglycemic event** to be considered severe the capillary glucose will exceed 500 mg/dL using a finger stick glucose meter reading (SMBG) and/ or patients may have ketones as evidenced by blood

ketone test of 0.6 mmol/L or higher or large urine ketones and/or the presence of nausea, vomiting or altered mental status. The following treatment protocol will be followed:

1. If patient is symptomatic (polyuria, polydipsia) or with concurrent illness, but capable of good communication, a phone contact to diabetologist is mandatory who will make the decision regarding a visit to see the study doctor or emergency department visit.
2. If symptoms are intense or the patient is incapable of good communication, immediate transport to emergency department should precede the phone contact.

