**Serious adverse event:** A serious adverse event (SAE) is an adverse event occurring at any time during the study that results in death, life-threatening adverse experience, inpatient hospitalization or prolongation of existing hospitalization, a persistent or significant disability or incapacity, or a congenital anomaly or birth defect. Severe hypoglycemic and severe hyperglycemic events will be considered an SAE. Other events may also be considered an SAE if, based on medical judgment, the event jeopardized the patient to the point of requiring medical or surgical intervention to prevent the occurrence of any of the conditions for an SAE listed above.

**Sentinel events** are defined as the subset of serious adverse events involving severe hypoglycemic (<50 mg/dL) or hyperglycemic (>500 mg/dL) occurrences AND any of the following: loss of consciousness, seizures, hospitalization, emergency room visit, professional intervention, or death.

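### Hyperglycaemia severity classes overlap at 301–500 mg/dL, and at 181–300 mg/dL nausea or vomiting fits only the severe class, so automatic SAE status is contradictory or symptom-driven

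*Protocol*

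**What the plan says.** Section 6.3 of the protocol sorts hyperglycaemic episodes into three classes.

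- **Mild:** glucose above 180 and up to 300 mg/dL, no ketones, "and the subject is not nauseated, vomiting or having an altered sensorium".
- **Moderate:** glucose above 300 and up to 500 mg/dL. No ketone value or symptom removes an episode from this class. Its first management step addresses symptomatic patients, and its second, for type 1 patients, reads: "If the ketonemia is equal or greater than 0.6 mM/L, the patient will be requested to change the infusion setting of the pump".
- **Severe:** the rule opens "event to be considered severe the capillary glucose will exceed 500 mg/dL using a finger stick glucose meter reading (SMBG) and/ or patients may have". The alternatives it then lists are a ketone level at the same 0.6 threshold, large urine ketones, and symptoms (nausea, vomiting, altered mental status).

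Section 7.1 repeats the severe definition for safety reporting. Its glucose criterion is worded "capillary glucose is above 500 mg/dL as revealed on an finger stick reading". The ketone and symptom criteria are then added as alternatives: "and/or a blood ketone test of 0.6 mmol/L or higher and/or the presence of nausea, vomiting or altered mental status". The section attaches two consequences. The first is automatic SAE status: "Severe hypoglycemic and severe hyperglycemic events will be considered an SAE". The second is the recording route: "These severe hyperglycemic events will be recorded on study case report forms according the procedures for SAEs in Section 7.3".

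**The concern.** A severity scale that decides SAE status should place each episode in one class. Here two of the severe criteria (ketones, symptoms) can be met at glucose values that the moderate class also claims. The mild class in turn sends every nauseated or vomiting patient out of its range, with only the severe class to receive them.

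The population makes this more than a drafting point. Section 4.2 lists nausea and vomiting among the symptoms that qualify a patient for entry, and it also requires an HbA1c of at least 8.0%. Raised glucose together with nausea is thus to be expected. The protocol gives no rule for telling a background gastroparesis symptom from a sign of metabolic decompensation.

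At stake are the SAE tabulations. Section 7.3 requires notification, a form and a narrative within 72 hours of a centre determining that an SAE has occurred, and a summary of all SAEs in the quarterly DSMB reports. Section 7.2 has adverse event rates compared by clinic. Section 8.4 proposes no formal stopping guideline, so the review after 10 completed patients and later monitoring rest on judgement of such summaries. Seven centres could code the same episode differently and each be following the text.

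**Working it through.** There is no sample-size or power figure to reproduce. The check is whether the three classes exclude one another.

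**Inputs.** Mild, moderate and severe rules from 6.3; severe rule and SAE status from 7.1.

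**Assumption, favourable to the protocol.** A hyperglycaemic event presupposes glucose above 180 mg/dL, the lower edge of the mild class. Neither severe definition states this.

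**Rules as conditions** (G = glucose in mg/dL, K = blood ketones, S = nausea or vomiting present):

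- Mild: 180 < G ≤ 300, and no ketones, and not S
- Moderate: 300 < G ≤ 500
- Severe: G > 180, and (G > 500, or K ≥ 0.6, or S)

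**Result**, checked at G = 181, 250, 301, 400 and 501, with K = 0 or 0.6 and S absent or present:

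| Glucose | Ketones | Nausea or vomiting | Mild | Moderate | Severe (SAE) |
|---|---|---|---|---|---|
| 181–300 | none | no | yes | no | no |
| 181–300 | none | yes | no | no | **yes** |
| 181–300 | 0.6 | either | no | no | **yes** |
| 301–500 | none | no | no | yes | no |
| 301–500 | none | yes | no | **yes** | **yes** |
| 301–500 | 0.6 | either | no | **yes** | **yes** |
| above 500 | either | either | no | no | yes |

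**Two defects follow.**

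1. *Double classification.* At 301–500 mg/dL, ketones of 0.6 or more, or nausea or vomiting, put the episode in both the moderate and the severe class. The conflict lies inside 6.3, between its moderate and severe paragraphs, as well as between 6.3 and 7.1. The two classes carry different management steps and different SAE status.
2. *Symptom-driven SAE.* At 181–300 mg/dL without ketones, adding nausea or vomiting moves the episode from mild straight to severe, and so to SAE, at a glucose value that otherwise ranks lowest.

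**Reach of the ketone overlap.** The moderate steps require ketone testing only in type 1 patients, and Section 3.2 provides for ketone-meter training only for them. Section 3.1 plans 20 type 1 patients out of 40. The metabolic panel in Appendix 11.2 also lists ketonaemia, at screening and weeks 12 and 24, so detection would be mainly, not solely, in type 1 patients. The symptom overlap has no such limit.

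**The case against.** The strongest reply is that the severe criteria grade an event that is already hyperglycaemic, so nausea at normal glucose is not captured. That is the sensible reading. A reader might infer from the and/or wording in 7.1 that nausea or vomiting qualifies alone at any glucose, but the term defined is a hyperglycaemic event and the 6.3 lead-in says the same. The table grants this, and both defects remain.

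A reader might also take the background rates in Section 2.1 (nausea 90%, vomiting above 80%) and infer that most of the study would generate SAEs: 0.90 × 40 = 36 and 0.80 × 40 = 32 patients. The documents do not support that. The rates describe gastroparesis in general, carry no time frame and do not measure symptoms coinciding with raised glucose. This study enrols mild to moderate cases. The figures are at most a ceiling on patients who could ever meet the symptom criterion, and say nothing about the number of SAEs.

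Other points on that side stand in part:

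- Sentinel hyperglycaemic events need glucose above 500 mg/dL plus a further consequence, so symptom-only cases cannot enter that definition.
- The primary outcome and the DSMB's 35% trigger concern hypoglycaemia only.
- SAE memos and narratives would let a reader recognise a symptom-only case one at a time. They do not correct the counts or the by-clinic rates.
- Section 7.2 limits adverse event recording to events thought to be associated with study participation, which may reduce the numbers. Section 7.1 makes severe hyperglycaemia an SAE without that condition, so the filter may or may not apply.
- Broad capture of symptomatic hyperglycaemia may be intended. That would explain the severe criteria, but not a moderate class that claims the same episodes.

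**Conclusion.** The point holds as a contradiction within Section 6.3 and between 6.3 and 7.1. Any episode at 301–500 mg/dL with ketones of at least 0.6, or with nausea or vomiting, has two classes with opposite automatic SAE status. Any episode at 181–300 mg/dL with nausea or vomiting is an SAE by elimination.

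The effect on SAE counts could be inconsistency between centres, inflation by background symptoms, or both. Its size cannot be estimated, because the protocol gives no frequency of nausea, vomiting or ketones during hyperglycaemia. The conclusion rests only on the class boundaries as written and on the assumption that an event needs glucose above 180 mg/dL. It affects the general SAE summaries, not the primary hypoglycaemia analysis or the sentinel-event definition. It should be corrected, but it does not undermine the study's main conclusion.

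**What to change.** Reconcile the mild, moderate and severe paragraphs of Section 6.3 with the severe-hyperglycaemia and SAE definitions of Section 7.1, so that each hyperglycaemic episode falls in exactly one class with one reporting route. Which clinical rule applies, and how background gastroparesis symptoms are to be treated, is for the clinical team.

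Add one field to the event form recording which criterion made a severe event qualify: glucose above 500 mg/dL, ketones, or symptoms only. Symptom-only cases can then be shown separately in the safety reports. The table layout can be left to the analysis plan, but the field has to be collected.

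The cost is amendment wording and one form field.
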